#### Secondary objectives

*(i) Cost-effectiveness:* We will use a Canadian healthcare system perspective in our cost-effectiveness analysis, with a 6-month time horizon. Costs will be assigned to health-resource utilization data for each exercise group and combined with data on cost per participant for the program. We will then sum costs of each intervention group and the costs of health-care utilization for each unit change in physical activity (min/wk. of moderate physical activity) to generate a cost per min/week of exercise. We anticipate that HB will be economically attractive. *(ii) Influence of person and setting-specific factors:* Association of person- and setting-specific characteristics with the primary outcome with be examined using repeated measures mixed effects linear regression but with the characteristic included as a factor in the model.

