## Methods & design

This is a pragmatic, randomized, parallel group trial to explore the relative effectiveness of two exercise delivery options (CB versus HB) among 60 people with MCI and mild dementia. The study will be conducted at two sites in Canada: Toronto (Sunnybrook Health Sciences Centre and University Health Network-Toronto Rehabilitation Institute) and Kitchener-Waterloo (University of Waterloo). Enrollment of participants began in September 2016 and is expected to continue until September 2018.

The study flow is shown in Fig. 1. Assessments will occur at baseline and immediately after the completion of the intervention. In addition to these assessments, physical activity, health status, and health care utilization will be reported monthly. Participants will be randomly assigned to CB or HB after baseline assessments, blocked by site, via a central internet randomization service (www.randomization.com). The randomization will be managed by a department research assistant not involved in the assessments and communicated to the participants directly or via the site research coordinator. Those who assess and those who analyze outcomes will remain blinded to allocation throughout and will report whether there was any indication of group allocation. In addition, analyses will be done by code (that is, Group ‘A’ and ‘B’) with code only revealed after analyses are complete. Due to the nature of the intervention, participants and exercise physiologists will not be blinded to group but participants will be blinded to the study hypotheses.

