### Measures

All participants will be assessed at the center at baseline and after the intervention. Participants will also complete a telephone assessment 1 month and 2 months into the program. Measures by time points are listed in Table 1. Assessors are blinded to group allocation throughout the study. Any possible disclosure will be noted.

**Table 1 Tab1:** Assessments by time point

	Baseline	1-month	2-month	Post-intervention
Participant Descriptors				
Participant information questionnaire	X			X
Height, weight, waist, BP	X			X
Medications	X			X
Physical activity history	X			
Social Support for exercise survey	X			X
BBAQ	X			X
Self-reported health	X	X	X	X
Falls	X	X	X	X
Secondary & Tertiary Outcomes				
RUD-Lite	X	X	X	X
PASE	X	X	X	X
ADAS-Cog	X			X
Stroop Test	X			X
Trails Making Task	X			X
Semantic Fluency	X			X
SPPB	X			X
DAD-6	X			X
EQ-5D	X			X
NPI-Q	X			X
6 min walk	X			X
25 ft. single & dual task	X			X
GAS	X			X
Primary Outcome				
Actigraph	1-week following			1-week following

*BP* blood pressure, *BBAQ* Barriers to Being Active Questionnaire, *RUD-Lite* Resource Utilization Dementia-Lite questionnaire, *PASE* Physical Activity Scale for the Elderly, *ADAS-Cog* Alzheimer Disease Assessment Scale-cognitive, *SPPB* Short Physical Performance Battery, *DAD-6* 6-item Disability Assessment for Dementia scale, *EQ-5D* Euro-Qol 5D, *NPI-Q* Neuropsychological Inventory, *GAS* Goal Attainment Scaling

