#### Secondary and tertiary outcomes

*Cost-effectiveness* will be determined by cost per unit change in physical activity (min/wk. of moderate physical activity). Participants will report health-care utilization each month, including visits to health care professionals, admissions or visits to the hospital, and laboratory work using the Resource Utilization Dementia (RUD)-Lite questionnaire, as employed in previous studies regarding exercise in cognitively impaired populations. [34, 35] Costs will then be assigned to health-resource utilization data (using a Canadian healthcare system perspective) and combined with the costs for each intervention group to generate a cost per min/week of exercise.

*Physical Activity* will also be reported at baseline, monthly during the intervention, and post-intervention using the Physical Activity Scale for the Elderly (PASE). The PASE is valid among older adults aged 65–100 years and for proxy responses by care partners. The PASE will be used to track physical activity change by month over the course of the intervention, to better understand the change in physical activity over time. In addition, it will be used to assess achievement of resistance training guidelines (2×/wk). [36]

*Cognitive Function* will be assessed with three measures. The Alzheimer Disease Assessment Scale-cognitive (ADAS-Cog) will be used to assess global cognitive function. [37] The ADAS-Cog is considered sensitive to the earliest cognitive changes in MCI and has been sensitive to exercise interventions. [24, 38] The Stroop Test will be used to measure executive function (inhibition), [39] which is arguably the cognitive domain most sensitive to exercise effects. [40] The Trail Making Task and Semantic Fluency will additionally be used to test additional components of executive function and language. [41, 42]

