### Sample size calculation

Sample size is based on the primary objective, to detect a significant difference in percent achievement of physical activity recommendations (continuous variable) between CB and HB groups over the intervention period. A recent Cochrane review of CB versus HB among older adults indicated that HB exercise had better physical activity achievement than CB, with an effect size of 0.8. [27] There were no studies that targeted people with cognitive impairment. To account for the possibility that cognitive impairment may reduce the feasibility of HB, we used a smaller effect size of 0.6, an alpha of 0.05 and a beta of 0.85 with two-group repeated measures MANOVA (within and between factors) to estimate a sample size of 39. We assumed 35% drop out, similar to our pilot work and to a previous study of exercise in people with MCI, [54] to bring the required sample size to 60.

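### The planned cost ratio merges programme cost with all-cause health-care cost and states no baseline term, so chance admissions can mask or reverse the delivery-cost difference

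*Protocol article*

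**What the plan says.** Under Secondary objectives (i), the article takes a Canadian healthcare-system perspective with a 6-month horizon. It costs the health-care use in each group, combines this with the programme cost per participant, and then: "We will then sum costs of each intervention group and the costs of health-care utilization for each unit change in physical activity". The result is a cost per min/week of moderate activity. The authors expect the home-based option (HB) to come out favourably against the centre-based option (CB).

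Under Secondary and tertiary outcomes, the health-care items are listed as "including visits to health care professionals, admissions or visits to the hospital, and laboratory work", with no restriction by cause. Table 1 schedules RUD-Lite (the "Resource Utilization Dementia-Lite questionnaire") at baseline, 1 month, 2 months and post-intervention.

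The trial is run "among 60 people with MCI and mild dementia". The allocation ratio is not given: "Participants will be randomly assigned to CB or HB after baseline assessments, blocked by site".

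**The concern.** The two halves of the ratio are treated differently. The denominator is a change from baseline. The numerator is a sum with no stated baseline term, and the text does not say whether use reported at the baseline RUD-Lite falls inside or outside that sum. For the primary and tertiary outcomes, by contrast, the article specifies a group-by-time model that uses the baseline value.

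The numerator also adds two quantities of very different precision. Programme cost is close to fixed by design: a weekly class of 3 to 5 people against a monthly call. All-cause health-care cost in a small sample can be dominated by a few admissions. Once the two are merged, a reader of the single ratio cannot tell a difference due to delivery mode from one due to a few hospital stays. The article says its results should inform cost-effective implementation, so the distinction matters.

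**Working it through.** The document states no figure for the cost analysis, so the only planned number to reproduce is the sample size, which sets the arm sizes.

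**Arm size.** The article reports a calculation "to estimate a sample size of 39" and adds: "We assumed 35% drop out, similar to our pilot work". Check: 39 / (1 − 0.35) = 60. With 1:1 allocation (assumed), that is 30 per arm randomised and about 20 per arm with complete data.

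**Noise from admissions.** Assumed, not in the document: admission risk p of 5-10% over the costing period, and cost C of $5,000-15,000 per admission. At most one admission per person is allowed and other health-care cost is ignored.

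- SD per participant = C × √(p(1 − p)).
- 95% half-width of the difference in arm means = 1.96 × SD × √(2/30).
- p = 0.05, C = $5,000: SD = $1,090; half-width = $551.
- p = 0.10, C = $15,000: SD = $4,500; half-width = $2,277.
- With 20 per arm these widen by √(30/20) = 1.22, that is by 22%.
- One admission moves an arm mean of 30 by C/30 = $167-500.

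**Delivery-cost gap.** Class size (3 to 5), the weekly 60-minute session and the monthly call come from the article. Assumed: 12-26 weeks, half-hour calls, and $50-100 per staff hour.

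- CB = weeks × rate / class size. HB = (weeks / 4.33) × 0.5 × rate.
- 12 weeks, class of 5, $50: 120 − 69 = about $50.
- 12 weeks, class of 4, $50: 150 − 69 = $81.
- 26 weeks, class of 3, $100: 867 − 300 = about $570.

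The smallest half-width ($551) is about equal to the largest gap (about $570). At most other points in these ranges the half-width is the larger, often several-fold.

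**How often arms differ by chance.** Exact binomial, no true difference, risk 5% to 10%:

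- 30 per arm: a difference of at least one admitted participant has probability 0.75 to 0.83; of at least two, 0.36 to 0.51.
- 20 per arm: 0.69 to 0.79, and 0.25 to 0.42.

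**Sensitivity to other assumptions.** Take 13-26 classes at $80-150 shared by four, and 3-6 calls at $30-60.

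- Low gap: 13 × 80/4 − 3 × 30 = $170. High gap: 26 × 150/4 − 6 × 60 = $615.
- Admissions needed to cancel the gap, 30 per arm: from 170/500 = 0.3 to 615/167 = 3.7.

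Simulation (100,000 trials per setting, gamma cost per admission with coefficient of variation 0.8, 30 per arm): suppose HB is truly cheaper by $200-800, risk is 5-15% and an admission costs $5,000-15,000. HB then looks dearer by chance in 2% to 46% of trials. At a $400 gap and $10,000 per admission, the figures are 26%, 33% and 37% for risks of 5%, 10% and 15%.

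**Value of baseline adjustment.** The standard error is multiplied by √(1 − r²), where r is the assumed correlation between baseline and follow-up cost. For r = 0.3, 0.5 and 0.6 the factor is 0.95, 0.87 and 0.80, a reduction of 5%, 13% and 20%. Even at r = 0.6, a half-width of $551-2,277 falls only to about $441-1,822.

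**The case against.** Several objections have force.

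- **All-cause cost is not an error.** It follows from the healthcare-system perspective, and exercise delivery could affect health-care use. This stands, and nothing here asks for it to be removed.
- **The article is condensed.** It does not say that baseline RUD-Lite will be ignored or that no interval will be given, and a fuller plan may contain both. This also stands: a missing interval alone would be no finding. What remains is the calculation the article does state, a pooled numerator with no baseline term turned into one ratio.
- **The size rests on outside inputs.** A reader might infer that one or two chance admissions will decide which option looks cheaper. The document does not support that, since it gives no admission risk, unit cost or programme cost. With cheap admissions and a large gap, the ranking holds.
- **The calculation is partial.** The gap counts staff time only, and facility and equipment costs at the centre would probably enlarge it. The same admission risk is used for 12 and 26 weeks. Only an extra admission in the cheaper arm can reverse a ranking; one in the dearer arm reinforces it. The ranking of cost per min/week also depends on activity change, which is not modelled here.
- **Baseline adjustment helps little.** It corrects imbalance in prior use and leaves most of the noise from admissions during follow-up.
- **Programme cost is already a separate input.** True, so showing it separately costs almost nothing.

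**Conclusion.** The point holds as a weakness of the stated calculation. Programme cost and all-cause health-care cost are merged into one cost per min/week, with no stated baseline term in the cost. Under the assumed risks and unit costs, uncertainty from admissions alone (half-width about $551-2,277 with 30 per arm) is about as large as, or larger than, a staff-time delivery gap of about $50-570. It can therefore reverse the apparent cost ranking. That is a possibility of uncertain size: across the assumptions tried, the chance of a reversed ranking runs from 2% to 46%.

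The documents do not support the stronger readings that chance admissions determine the result, that counting all-cause use is wrong, or that baseline RUD-Lite will certainly go unused. The expectation that HB will be favourable carries no test or threshold, so no decision rule is at issue.

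**What to change.** In Secondary objectives (i):

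1. Report the HB-CB difference in programme cost on its own, beside the total-cost result. Keep all-cause health-care cost in the total.
2. Compare health-care cost after randomisation with baseline RUD-Lite cost as a covariate, and state that the baseline period is outside the sum. The gain is modest, about 5-20% off the standard error at correlations of 0.3-0.6.
3. Give participant-level bootstrap intervals for the cost difference and for the joint cost-activity result.

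This costs a few lines of text and a little more analysis, with no new data. The drawback is that programme cost alone ignores any downstream savings, which is why both results should be shown.

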Trials of exercise interventions among people with MCI or dementia indicate that both CB and HB exercise can be effective for improving cognitive, physical, and other outcomes (for example, [23, 26]). It is possible that the most effective option will not be uniform even within this clinical group but may depend further on the individual (e.g., degree of care partner support, diagnosis (i.e. MCI vs dementia), severity of deficits) and the context (e.g., weather, proximity to facilities). Consequently, the aim of this study is to compare the effectiveness of CB versus HB exercise programs in achieving aerobic exercise guidelines (percent of 150 min per week of moderate intensity activity) among people with MCI and mild dementia. Secondary objectives will compare the cost-effectiveness of the interventions and examine the influence of individual and environmental factors on achievement of the primary outcome. Exploratory objectives will compare the effect of CB and HB exercise on physical function, cognitive function, vascular health, quality of life, instrumental activities of daily living (IADLs), mood, and individual goal attainment. Based on prior results among healthy older adults, [27] we hypothesize that participants assigned to the HB exercise group will have a higher percent achievement of physical activity guidelines compared to the CB exercise group. Conversely, we hypothesize that the CB group will experience greater gains in physical function than the HB group.

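### The cost-effectiveness result is worded as each arm's cost per unit change in activity, and this can rank CB and HB differently from the randomised comparison

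*Protocol article*

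**What the plan says.** The Background states the aim as a comparison: "Secondary objectives will compare the cost-effectiveness of the interventions". Two later sections then define the measure.

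- Under Secondary and tertiary outcomes, cost-effectiveness "will be determined by cost per unit change in physical activity", in minutes per week of moderate activity. Health-care costs from the RUD-Lite questionnaire are "combined with the costs for each intervention group to generate a cost per min/week of exercise".
- Under Secondary objectives (i), the setting is given as "We will use a Canadian healthcare system perspective in our cost-effectiveness analysis, with a 6-month time horizon". The calculation is a group total related to a change in activity, and its denominator and result are worded as "for each unit change in physical activity (min/wk. of moderate physical activity) to generate a cost per min/week of exercise". The expected result is also stated: "We anticipate that HB will be economically attractive".

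Neither section mentions a difference in cost between the arms, a difference in activity between the arms, or a ratio of the two. The article says that EQ-5D utilities could support a cost-utility analysis, but it gives no incremental measure there either.

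**The concern.** The question is comparative: if one delivery option costs more, what does the extra money buy? The answer needs the difference in cost and the difference in activity between the randomised arms. The text instead takes each group's total cost and relates it to a change in activity.

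Neither part of such a ratio isolates the effect of the delivery option. There is no untreated arm, so the change within an arm includes whatever would have happened anyway. The article gives reasons to expect such change. It records weather as a possible influence on activity, and it excludes people who already exercise at moderate intensity three or more times a week, which makes upward regression to the mean plausible. The cost side includes visits, admissions and laboratory work, much of which may be background cost in this population. In a between-arm difference these shared amounts cancel. In two separate ratios they do not.

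At stake is the headline economic conclusion. The option reported as cheaper per minute could depend on quantities that are the same in both arms.

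**Working it through.** The article gives no cost, effect or ratio for this analysis, so there is no figure to reproduce. All costs and gains below are assumptions, chosen only to show how the measure behaves.

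Formulas, with C the mean cost per participant and E the mean change in min/week:

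- average ratio, as worded: C_arm / E_arm
- incremental ratio: (C_CB − C_HB) / (E_CB − E_HB)

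**Step 1: a change shared by both arms.** Assume C_HB = 300 and C_CB = 900.

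| Case | E_HB | E_CB | HB average | CB average | Incremental |
|---|---|---|---|---|---|
| No shared change | 10 | 40 | 300/10 = 30.0 | 900/40 = 22.5 | 600/30 = 20 |
| +20 in both arms | 30 | 60 | 300/30 = 10.0 | 900/60 = 15.0 | 600/30 = 20 |

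The lower average ratio moves from CB to HB, although the randomised difference is 30 min/week in both rows. The switch comes at a shared change of 5 min/week, where 300/15 = 900/45 = 20.

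**Step 2: a cost shared by both arms.** Assume C_HB = 200, C_CB = 600, E_HB = 30 and E_CB = 40, and add the same health-care cost H to each arm.

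| H | HB average | CB average | Incremental |
|---|---|---|---|
| 0 | 200/30 = 6.7 | 600/40 = 15.0 | 400/10 = 40 |
| 1,000 | 1,200/30 = 40.0 | 1,600/40 = 40.0 | 400/10 = 40 |
| 2,000 | 2,200/30 = 73.3 | 2,600/40 = 65.0 | 400/10 = 40 |

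The ranking reverses once H exceeds 1,000. The incremental ratio does not move.

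**Step 3: dominance.** Assume C_HB = 300, C_CB = 900, E_HB = 45 and E_CB = 40. HB is cheaper and gains more. The averages are 300/45 = 6.7 and 900/40 = 22.5, so they agree with dominance. When both changes are positive this always holds, because the dominant arm has the smaller numerator and the larger denominator.

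The problem is therefore confined to the trade-off case, where the dearer arm gains more, and to cases where an arm's change is not positive.

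**The case against.** **The wording is loose.** The article never defines the unit of change as change from baseline within an arm, and an incremental ratio may have been intended. This stands as a limit on how firmly the point can be put. The per-arm reading is still the natural one, because costs are summed by intervention group and no between-arm difference appears. If an incremental ratio was meant, the same sentences need the same correction.

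**An article may leave economic detail to a fuller plan.** This also stands. The absence of bootstrap intervals, net benefit or a value per minute is not a fault here. The estimator, however, is not missing. It is stated in two sections, and a plan that follows them would carry it forward.

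**The protocol expects HB to achieve more.** The Background hypothesises higher guideline achievement with HB. If HB is also cheaper, it dominates and the ratios point the right way. The examples in which the ranking reverses assume that CB gains more, which is the opposite of that hypothesis. A reader might infer that the planned ratio can never show which option is cost-effective. Dominance shows that this is too strong.

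**A conclusion in favour of HB might look built in.** A reader could infer this from the stated expectation and from HB's presumably lower programme cost. The arithmetic does not support it. The ratio favours the dearer arm in the first row of step 1 and in the last row of step 2.

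**The ratio might look too unstable to use.** With 20 per arm, an assumed SD of change of 60 to 90 min/week and a true mean change of 15, an arm's mean change is zero or negative in about 13% to 23% of trials. At a true mean change of 30 the figure is about 1% to 7%. The documents fix neither the mean nor the SD. Intention-to-treat analysis with multiple imputation would keep about 30 per arm (60/2). An incremental ratio has the same weakness when the activity difference is near zero. Instability is therefore a reason to report uncertainty carefully. It does not by itself decide between the two measures.

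**The incremental estimate could be recovered.** The primary model's group-by-time term gives the randomised difference in percent achievement, and one percentage point is 1.5 min/week (150/100). With costs reported by arm, the point estimate is simple arithmetic. This limits the harm, but the planned headline figure would still be the per-arm ratio.

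**Conclusion.** The point holds for the measure as it is most naturally read. The objective is comparative, and the stated ratio does not preserve the randomised comparison. In the assumed examples the ranking reverses with a shared change of more than 5 min/week, or with a shared cost of more than 1,000 per participant, while the incremental ratio stays fixed at 20 and 40 respectively. Those thresholds belong to the assumed inputs and do not predict the trial's result.

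The conclusion rests on two things: reading the ratio as per arm, and the possibility of a trade-off in which the dearer option gains more. It concerns a secondary objective and leaves the primary analysis untouched. The text should be corrected, because the error lies in a stated definition and is cheap to remove.

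**What to change.** In both Secondary and tertiary outcomes and Secondary objectives (i):

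1. Define the comparative result as the randomised between-arm difference in mean cost and in mean activity (min/week), each adjusted for its baseline value.
2. Report it as an incremental ratio, or state dominance where one arm is cheaper and gains more.
3. Give uncertainty jointly for cost and effect. Because the incremental ratio is unstable when the activity difference is near zero, bootstrapped net benefit over a range of values per min/week is a suitable form.
4. Keep cost per minute within each arm as a descriptive figure only.

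The cost is a change of wording and slightly more analysis. RUD-Lite is already collected at baseline, months 1 and 2 and post-intervention, and the activity monitor is worn after the baseline and post-intervention assessments. The one drawback is a headline figure that is less simple than a single cost per minute.

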#### Primary objective

Mixed effects linear regression will be used to analyze differences in the primary outcome (percent achievement of physical activity recommendations) as a function of group (CB, HB), time (baseline, follow-up and interim month 1, month 2 where relevant), and group x time. A random effect for participants and site (CB) will be included in the models.

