#### Tertiary objective

Change in each tertiary outcomes between T1 and T2 will be examined using mixed effects linear regression as a function of group, time, and group x time interaction. A random effect for participants and site will be included in the models.

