## Discussion

This study will examine the effects of CB versus HB exercise on physical activity as well as cost, cognitive function, physical function and health, functional ability, apathy and depressive symptoms, and quality of life among people diagnosed with MCI or mild dementia. We will consider whether outcomes or the relative effectiveness of the interventions varies according to individual or environmental factors.

The prevalence of dementia worldwide is expected to nearly triple in the next 35 years. [1] Increasing research suggests that exercise can improve cognitive function, physical function, as well as functional abilities among people with MCI and dementia. [5] Despite these benefits, people with MCI and dementia are frequently inactive. [17, 18] Effective strategies to increase exercise in this group have not been identified and are needed to leverage exercise-related benefits. [22] Most often, exercise trials have used either highly controlled interventions, which are not reflective of community exercise opportunities, or occur within residential care. [5] Neither offers insight into effective strategies for community-dwelling adults with cognitive impairment. People with cognitive impairment have several differences (cognitive function, physical function, mood, mobility) that may alter the feasibility of exercise delivery options compared to older adults more generally and may make some programming options less accessible. [19–21, 56, 57] This study takes a pragmatic approach to evaluating the effectiveness of exercise delivery options as could be available in the community among people with MCI or mild dementia to understand how well, in whom, and where each option will work in ‘real-life’.

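### The model for person and setting factors names no interaction, so it shows who is more active overall, not who improves or whether the CB-HB difference varies

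*Protocol article*

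**What the plan says.** The primary model (Analysis, Primary objective) has group, "time (baseline, follow-up and interim month 1, month 2 where relevant), and group x time", with random effects for participant and site. The tertiary outcomes are modelled "as a function of group, time, and group x time interaction".

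For person and setting factors, Secondary objectives (ii) gives the target as "Association of person- and setting-specific characteristics with the primary outcome". The method is the repeated-measures mixed model, "but with the characteristic included as a factor in the model". No product of the characteristic with group or time is written.

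The aims are worded at two strengths:
- **Formal objective (Background; the Abstract is similar):** "examine the influence of individual and environmental factors on achievement of the primary outcome".
- **Discussion:** "We will consider whether outcomes or the relative effectiveness of the interventions varies according to individual or environmental factors". The approach is also meant "to understand how well, in whom, and where each option will work" in practice.

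The Background supplies the rationale: "It is possible that the most effective option will not be uniform even within this clinical group but may depend further on the individual", and on the context. Later in the Discussion there are arm-specific examples: an unsupportive or unwell care partner may restrict exercise outside the home, and CB may appeal more when travel is short.

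**The concern.** Whether CB or HB works better for particular people or places is a question about how the group x time effect changes with the characteristic. A characteristic added without a product term cannot answer it, because the model then holds one CB-HB difference in change for everybody.

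The narrower objective is also served poorly. Table 1 places the activity monitor only after the baseline assessment and after the post-intervention assessment. A main effect over those two occasions mixes activity before the intervention with activity after it. A characteristic that marks people who were already more active would look influential even if it had nothing to do with response to either programme.

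At stake is the reading of a secondary result. A characteristic that predicts activity equally in both arms could be taken as a guide to choosing between them, and a real modifier would not be estimated at all. The primary comparison is not affected.

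**Working it through.** **1. What the stated model estimates.** Write G for group (0/1), T for time (0 baseline, 1 follow-up) and X for a binary characteristic. The additive reading is

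E(y) = b0 + b1·G + b2·T + b3·G·T + b4·X.

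The difference between arms in change is b3 at X = 0 and b3 at X = 1. The change within an arm does not involve X either. The coefficient b4 is a shift common to both arms and both times.

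**2. A worked reversal.** Take two equal arms and X split 50:50. Let the arm effect on change be -0.6 at X = 0 and +0.6 at X = 1, with no other effect of X.
- Expected b3 = (-0.6 + 0.6)/2 = 0.
- X shifts the outcome by 1.2 in one of two arms at one of two times, so expected b4 = 1.2 × 1/2 × 1/2 = 0.30.
- With X x G x T and its lower-order terms, the effect at X = 0 is -0.6 and the three-way term is 1.2.

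One simulated data set of 4,000 participants agrees. The additive model gave b3 = 0.04 and b4 = 0.30. The crossed model gave -0.49 at X = 0 and a three-way term of 1.05, within sampling error of 1.2. The additive model hides a complete reversal and reports an overall association instead.

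**3. The plan's own sample size.** Inputs from Sample size calculation: effect size 0.6, alpha 0.05 (taken as two-sided), 0.85 printed as beta and read as power, 39 before dropout, 35% dropout.
- 39/(1 - 0.35) = 60, as stated.
- The 39 depends on a within-person correlation that is not given. Under an assumed correlation of 0.8, the total is 36 (baseline-adjusted) or 40 (change score), so 39 is attainable but not confirmed.

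**4. Precision of an interaction, taking the stated power as true.**
- Implied standard error of the overall effect: 0.6/(1.960 + 1.036) = 0.200.
- For a characteristic with share p, balanced across arms, the standard error of the difference in effects is 0.200 × √(1/p + 1/(1-p)).

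| Split | Multiplier | SE | Detectable at 85% power | Power for a 0.6 difference | Completers needed for 0.6 |
|---|---|---|---|---|---|
| 50:50 | 2.00 | 0.400 | 1.20 | 32% | 4 × 39 = 156 |
| 30:70 | 2.18 | 0.437 | 1.31 | 28% | 4.76 × 39 ≈ 186 |

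**5. Without the repeated-measures gain.** In an unadjusted comparison at follow-up with 39 completers, the overall effect detectable at 85% power is about 0.99 SD. Doubling it gives about 1.97 SD for a 50:50 interaction. This is a pessimistic bound, because the plan uses baseline as well as follow-up.

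**The case against.** **The objective asks only for association.** The Background objective, the Abstract and the analysis section agree on influence or association, and a factor in the model can address that. This largely stands. A reader might infer that the secondary analysis fails its own formal objective on effect modification. The documents do not support that: the Background sentence about the best option differing between people is rationale, and the commitment to examine relative effectiveness is in the Discussion. Even there, the part about outcomes varying is covered by the stated model. What remains against the formal objective is weaker: influence on achievement is more usefully read as who improves, and a main effect averaged over baseline does not show that.

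**The wording may mean a crossed factor.** The article never says main effect, and the sample size section uses factors in the design sense. The ambiguity is real. But the primary and tertiary models write out group x time, no such term appears here, and the stated target is association. The additive reading is the natural one, though not the only one.

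**Such detail may belong in the analysis plan.** An article may leave the model form open. This one gives a form, and as worded it does not reach a question the same article says it will consider.

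**The remedy has little power.** True: at 28% to 32% power for a 0.6 difference, most real modifiers would not reach significance. That argues for intervals and an exploratory label, not for a model that cannot estimate the quantity. Nor does the article say that associations will be used to direct people to CB or HB; that misuse is a risk, not a plan.

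**Conclusion.** The point holds in a limited form. Read as additive, the model for secondary objective (ii) describes who is more active on average across arms and times. It cannot show who improves, and it cannot address the Discussion's question about relative effectiveness. It can serve a plain association question.

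A reader might take 2 SD as the smallest detectable interaction in this trial. That figure belongs to an unadjusted follow-up comparison. On the article's own power claim for the repeated-measures design, it is about 1.2 for an even split and 1.31 for 30:70. These figures assume a binary characteristic balanced across arms, a two-sided 5% test, and exactly 85% power for 0.6 with 39 completers.

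This is a secondary analysis that should be corrected. It does not touch the primary comparison.

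**What to change.** In Secondary objectives (ii):
- List a small set of baseline characteristics in advance.
- For relative effectiveness, fit characteristic x group x time with all lower-order terms. Report the CB-HB difference in change at each level, with confidence intervals, and label the results exploratory.
- For predictors of improvement, report characteristic x time instead of the main effect.

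If the investigators want only predictors of activity, reword the Discussion aim to say so.

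The cost is a few lines of text and no new data. The downside is wide intervals, which should be stated beforehand using the figures above.
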